### Study design and intervention

A flowchart of the study design is shown Fig. 1. Flow-diagram of study process is shown in Fig. 2. In the first phase of this study, we will screen 300 patients with NAFLD based on the inclusion criteria mentioned above. Then, those who meet the criteria will be included in the study. All participants will be asked to complete and sign the written informed consent. Before the start of intervention, all study participants will be in a 2-week run-in period, during which four 24-h food recalls (two working days and one non-working day) will be used to collect dietary information. In addition, subjects will be requested to record their physical activity for two days (one working day and one weekend day) during this period. Further information about demographic characteristics, past medical history, medication use as well as socioeconomic status (SES) will be collected in this period through the use of a comprehensive questionnaire in a face-to-face interview. Anthropometric indices, blood pressure, liver enzymes, insulin resistance, hepatic steatosis, liver fibrosis and lipid profile will be evaluated at study baseline. Then study participants will be classified into blocks based on age (20–40/ 40–60 years old), sex (male, female) and BMI (25–30/ 30-35 kg/m^2^). Therefore, the size of each block will be 2 people with the same age, sex and BMI. These participants will then be randomly assigned into intervention and non-intervention groups. Randomization will be done by a third person, who is not aware of the study aims and groups. The first person (say A) in a block will be assigned into the intervention group and the second person (say B) in that block will be assigned into the control group. All participants, study personals and laboratory staffs will be blind to the intervention. Participants in the intervention group will consume 300 g/d of probiotic yogurt containing 10^6^ cfu/g of Lactobacillus acidophilus and Bifidobacterium lactis strains for 12 weeks, while participants in the control group will consume 300 g/d of plain yogurt daily (without any added probiotics) for 12 weeks. Yogurt packages will be distributed to participants every two weeks. The appearance, packaging and taste of yogurts will be the same. Quality control of these yogurts in terms of colony forming units of live bacteria and other nutritional values will be evaluated before the study. In order to comply with the ethical requirements in research, all patients will receive a weight loss diet after ending the study. Participants will be asked not to change their routine lifestyle, dietary habits, and medicines throughout the study. All study outcomes will be examined again at the study end. The study was designed according to the Standard Protocol Items: Recommendations for Interventional Trials (SPIRIT) 2013 shown in Fig. 3.

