**Methods:**

Sixty-eight patients with NAFLD will be recruited in this study. After block matching for sex, BMI and age, patients will be randomly assigned to receive 300 g/d probiotic yogurt containing 10^6^ cfu/g of Lactobacillus acidophilus and Bifidobacterium lactis strains or 300 g/d plain yogurt daily for 12 weeks and those in the control group would receive similar amounts of plain yogurts. Weight, height, and waist circumference will be measured at study baseline and after the intervention. Biochemical indicators including plasma glucose, serum insulin, lipid profile, liver markers (ALT, AST and GGT) will be examined at study baseline and at the end of the trial. Insulin resistance and insulin sensitivity will be determined using the HOMA-IR and QUICKI equation. The degree of steatosis and hepatic fibrosis will also be assessed at the beginning and end of the intervention by the same gastroenterologist using elastography with fibroscan.

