Despite several strengths of our study protocol including stratified permuted block randomization and double-blind, placebo-controlled design and conducting the study on newly diagnosed NAFLD patients by fibroscan, some limitations must also be taken into account: We will examine the compliance in this study through collecting dietary intake information by questionnaires. Due to limited funding, we are unable to examine gut microbiota and serum trimethylamine N-oxide (TMAO) as a biomarker for assessment of compliance in this study. We also use probiotic strains available in the food market and did not focus on specific strains that might have different effects. Future studies should examine the effect of foods fortified with specific probiotic strains on steatosis and fibrosis in patients with NAFLD. In addition, another concern might be a limited duration of intervention in this study which would be for 12 weeks. Although one might assume this time period too short for our intervention to affect liver fibrosis, other studies have applied almost the same duration for assessing the effect of intervention of fibrosis among patients with NAFLD.

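### Allocation follows baseline measurement and a two-person match, so if pairs form as patients arrive, the probiotic arm could start treatment on an older baseline, and unmatched patients have no stated allocation route

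*Protocol article*

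**What the plan says.** All of the following is in the protocol article. Study design and intervention gives the steps in this order.

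- There is a 2-week run-in, and outcomes are measured: "hepatic steatosis, liver fibrosis and lipid profile will be evaluated at study baseline".
- Grouping follows: "Then study participants will be classified into blocks based on age (20–40/ 40–60 years old), sex (male, female) and BMI". BMI is split at 30, so there are 2 × 2 × 2 = 8 cells.
- Blocks are pairs: "Therefore, the size of each block will be 2 people with the same age, sex and BMI".
- Allocation comes after that: "These participants will then be randomly assigned into intervention and non-intervention groups".
- Within a pair the rule is fixed: "The first person (say A) in a block will be assigned into the intervention group and the second person (say B) in that block" goes to control.

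The abstract (Methods) has the same sequence: "After block matching for sex, BMI and age, patients will be randomly assigned". The Discussion, however, counts "stratified permuted block randomization and double-blind, placebo-controlled design" among the strengths of the trial. The Outcomes section places measurements at baseline and at the end of the trial only. Both arms take yogurt for 12 weeks.

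**The concern.** When allocation depends on a completed pair, the first patient in a cell cannot be allocated until a second patient of the same age band, sex and BMI band has also finished run-in and baseline. The second patient has no such wait. If the first is always sent to probiotic yogurt, the wait falls in one arm only.

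The interval between the two outcome measurements would then be the wait plus 12 weeks for probiotic patients, against 12 weeks for controls. Any drift in weight, diet, season or disease during the wait would enter the probiotic change and not the control change. Adjusting for the baseline value, as the Statistical analysis section plans, corrects for differences in level but not for differences in elapsed time. An older baseline also predicts the final value less well, which costs precision.

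Matching in pairs raises a second problem. A cell with an odd number of patients leaves one person who has completed run-in and baseline and has nobody to be allocated with. The article does not say what happens to that person.

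**Working it through.** **Inputs from the article.** 34 patients per group, so 68 in total (Participants); 8 cells and pairs of 2 (Study design and intervention); 12 weeks of treatment.

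**Assumptions.** The recruitment period is not stated, so 13, 26 and 52 weeks are used, with 4 weeks as a short case. Arrivals are spread evenly over the period. Consecutive patients in the same cell form a pair, and the first is held until the second arrives.

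**Wait of the first member, by formula.** Equal cells hold 68 / 8 = 8.5 patients on average. With n arrivals spread at random over T weeks, the mean gap between neighbours is T / (n + 1) = T / 9.5.

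- T = 13: 13 / 9.5 = 1.4 weeks
- T = 26: 26 / 9.5 = 2.7 weeks
- T = 52: 52 / 9.5 = 5.5 weeks

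**By simulation** (3,000 runs; the unequal cells have shares from 25% down to 4%):

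| Recruitment (weeks) | Mean wait, equal / unequal cells (weeks) | Mean longest wait in a trial, equal / unequal (weeks) | First members waiting over 4 weeks, equal / unequal |
|---|---|---|---|
| 4 | 0.41 / 0.38 | 1.6 / 1.8 | 0% / 0% |
| 13 | 1.34 / 1.25 | 5.3 / 5.9 | 5% / 5% |
| 26 | 2.69 / 2.49 | 10.6 / 11.8 | 23% / 19% |
| 52 | 5.40 / 4.97 | 21.4 / 23.7 | 48% / 42% |

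The formula and the simulation agree.

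**Interval between measurements under this reading** (equal cells, final measurement at 12 weeks of treatment). Probiotic: 12 + 1.3 = 13.3, 12 + 2.7 = 14.7 or 12 + 5.4 = 17.4 weeks for 13, 26 or 52 weeks of recruitment. Control: 12 weeks.

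**The same difference under other readings.**

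- All patients are measured and then paired in one batch: older baselines are not tied to either arm, so the pairing-related difference is 0.
- The first member starts at once because the arm is already fixed: there is no wait, so the difference is 0.
- Order within the pair is random, as permuted blocks imply: any wait falls on both arms alike, so the expected difference is 0.

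**Unmatched patients.** Each cell has an odd count with probability close to one half, so about 8 × 0.5 = 4 are expected. The simulation gives 4.0. The maximum is one per cell, or 8.

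**If the first member starts at once**, every unmatched patient is already on probiotic. With 4 such patients there are (68 − 4) / 2 = 32 pairs, giving 36 against 32. With 8 there are 30 pairs, giving 38 against 30.

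**The case against.** The strongest reply is that the difference between arms needs conditions the article never states: pairs form as patients arrive, the first member is held, first means first in time, and the baseline is neither repeated nor timed close to the start. Study design and intervention can also be read as a batch flow: 300 are screened in a first phase, then eligible patients are run in, measured and blocked. Under a literal fixed rule the first arrival's arm is already known, so no wait is logically needed. Under true permuted blocks the order is random. The flow and schedule figures are not available here and may show the timing. The clearer fault in the same section is the fixed first-to-intervention order itself, which conflicts with random assignment.

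Most of this stands, and it makes the timing difference conditional. It does not remove the point. Starting the first member at once departs from the article's own sequence of matching before assigning. Random order within the pair would balance a wait without removing it. The article describes one procedure in Study design and intervention and names another in the Discussion.

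A reader might infer that the 12-week change certainly covers unequal periods in the two arms. The documents do not support that: treatment is 12 weeks in both, and only the gap from baseline to start could differ. A reader might also infer that batch pairing makes every baseline out of date and so biases the result. That is not supported either, because baselines could be taken shortly before blocking, and drift shared by both arms cancels in the comparison.

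The count of about 4 unmatched patients assumes that recruitment stops at exactly 68. Partners could be sought in the wider screened pool, at the price of a longer wait.

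**Conclusion.** The point holds as a weakness of the match-then-assign procedure, with a conditional effect on timing. Followed as written with patients enrolling over time, the procedure gives the probiotic arm a longer gap from baseline to first yogurt, by a mean of about 1.3, 2.7 or 5.4 weeks for recruitment over an assumed 13, 26 or 52 weeks. Under batch pairing, immediate start or random order within pairs, the difference is zero, so the supported range starts at 0. The article gives no rate of drift for steatosis or any other outcome, so the wait cannot be turned into a bias in dB/m or a loss of power.

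The missing route for unmatched patients (about 4 expected, at most 8, if 68 are enrolled) does not depend on whether pairing is sequential or in one batch. The conflict between the fixed order and the permuted blocks claimed in the Discussion is plain from the text.

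**What to change.** Replace matching followed by assignment with single allocation. At the end of the run-in, soon after baseline measurement, allocate each patient from a concealed, pre-generated random list stratified by age band, sex and BMI band. Nobody then waits for a partner, no arm is tied to arrival order, and a patient in an odd-count cell is allocated like any other. Rewrite the allocation text in Study design and intervention so that it agrees with the permuted blocks named in the Discussion, and bring the abstract into line.

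The cost is a change of wording and the preparation of the list, with no added measurements. The downside is slight imbalance within some cells; if blocks of two are kept in the list, no cell ends more than one patient out of balance.

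The Trial status section says recruitment began in December 2021. For patients already allocated, the authors should state how pairs were actually formed and report the gap from baseline to first yogurt by arm.

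### The only allocation rule stated is fixed by position in a matched pair, which contradicts the claimed permuted-block randomisation

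*Protocol article*

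**What the plan says.** The mechanism is in the protocol article, Study design and intervention. After screening, consent, a two-week run-in and baseline measurement, the article continues: "Then study participants will be classified into blocks based on age", sex and BMI, each in two classes. The age classes share the value 40 and the BMI classes share the value 30. It then states that "the size of each block will be 2 people with the same age, sex and BMI".

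Two sentences describe the assignment in general terms: "These participants will then be randomly assigned into intervention and non-intervention groups", and "Randomization will be done by a third person, who is not aware of the study aims and groups". The rule itself follows: "The first person (say A) in a block will be assigned into the intervention group". For the other member of the pair, the article says that "the second person (say B) in that block will be assigned into the control group".

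Two other places characterise the method. The Abstract (Methods) says that patients are assigned at random after block matching. The Discussion lists "stratified permuted block randomization and double-blind, placebo-controlled design" among the strengths of the design.

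**The concern.** In permuted-block randomisation with blocks of 2, each block is drawn at random as AB or BA. The rule in the article makes every block AB. That is a fixed assignment by position, and it cannot be the method the Discussion claims.

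At stake is the basis of every between-group comparison in the Statistical analysis section. Those tests support a causal reading because chance alone decides who gets which yogurt. If position in the pair decides, whatever determines position is tied to treatment arm, and no later adjustment restores randomisation. A fixed rule can also be foreseen. Someone who knows it and can influence who is placed first, or which pair a patient joins, can influence the arm.

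**Working it through.** **Inputs**
- Planned size: 34 per group, 68 in total (Participants).
- Block size: 2, so 68 / 2 = 34 pairs.
- Strata: 2 age classes × 2 sexes × 2 BMI classes = 8.
- Rule: first member to intervention, second to control (Study design and intervention).

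The plan gives no figure of its own on this point to reproduce.

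**Step 1. Stated rule against claimed method**

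| | Rule as written | Permuted blocks of 2 |
|---|---|---|
| P(intervention), first member | 1 | 0.5 |
| P(intervention), second member | 0 | 0.5 |
| Possible orders per pair | 1 (AB) | 2 (AB, BA) |
| Possible sequences over 34 pairs | 1^34 = 1 | 2^34 = 17,179,869,184 |

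Given the pairs and the order within them, the written rule leaves nothing to chance. The columns would agree only if a random draw decided who counts as first. The text describes no draw, list or other device that does so.

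**Step 2. If the labels A and B were drawn at random**

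Suppose earlier assignments in a block become known and the block size is known.
- Block of 2: the first assignment is a guess (1/2) and the second is certain (1). Share certain = 1/2 = 50%. Expected correct guesses = (1/2 + 1) / 2 = 75%.
- Block of 4: the fourth is always certain, and the third is certain when the first two agree, which has probability 1/3. Share certain = (1 + 1/3) / 4 = 33%. Expected correct guesses = (1/2 + 2/3 + 2/3 + 1) / 4 = 71%.
- Block of 6, by enumeration of all orders: 25% certain, 68% correct guesses.

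The written rule gives 100% on both measures to anyone who knows the rule and the position. A random order within fixed pairs removes the determinism, but one disclosed assignment still reveals the partner's.

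**Step 3. The strata**

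A patient aged exactly 40, or with a BMI of exactly 30, fits two classes and so could be placed in more than one block. This is minor in itself. It matters here because placement in a block determines the arm under the written rule.

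**Step 4. The allocator**

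The third person is said to be unaware of the groups, yet the rule has someone assign patients to named groups. Coded packages would reconcile the two statements, but the article does not describe any.

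**The case against.** The strongest reply is that the sentence is loosely worded. The text just before it says that assignment is random and is done by a third person, and the Abstract and the Discussion agree. A and B may be labels produced by a draw that the article did not spell out. An article condenses the full protocol, and its figures are not shown here.

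Part of this stands. The article never says what makes someone first. A reader might infer order of entry, but that is not stated. A reader might also infer that the arm is known before consent. The documented sequence contradicts this, because consent, run-in and baseline all precede the forming of blocks. If both members of a pair are enrolled before assignment, foreknowledge cannot affect who is enrolled.

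Nor do the documents support the inference that allocation is unconcealed or that blinding fails outright. A third person allocates, and the two yogurts are to match in look, packaging and taste. Blinding is at risk only for someone who knows both the rule and a patient's position, and nothing says that assessors or laboratory staff would know either. Silence on concealment detail is no finding in a condensed article.

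The reply does not remove the contradiction. The article did not simply omit the mechanism. It states one, and that one is deterministic. The random draw has to be supplied by the reader.

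**Conclusion.** The point holds as a contradiction between the stated rule and the claimed method. As written, allocation is deterministic given position in the pair (one possible sequence against 2^34) and foreseeable before assignment by anyone who knows the rule and that position. If the rule was followed literally, the trial is not randomised by permuted blocks. If a draw was in fact used, the text is wrong, and the weakness of fixed pairs remains: up to 50% of assignments are certain in advance if earlier ones become known. The documents do not settle which of these applies, so this does not establish that the trial was conducted without randomisation.

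A reader might also infer unequal arms, because an unfilled pair would always add its one patient to intervention. With 68 patients spread evenly at random over 8 strata (an assumption), about 4 strata would have odd counts. Four odd strata give 36/32, and the extreme of 8 gives 38/30. The documents do not support this as a prediction. It requires incomplete pairs to be allocated, whereas matching into complete pairs yields the stated 34/34. Even at 36/32 the effective size per arm would be 2 × 36 × 32 / 68 = 33.9 against 34, a negligible loss. Imbalance is not part of the finding.

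**What to change.** Replace the first/second rule with a computer-generated list of random permuted blocks within the age, sex and BMI strata. Draw the order at random in each block, preferably with block sizes that vary at random (for example 2 and 4). The existing third person holds the list and releases assignments one at a time as coded yogurt numbers, at the point after consent and baseline where the article already places assignment. Coding also explains how that person can allocate without knowing the groups.

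Define strata that do not overlap, for example under 40 against 40 and over, and BMI under 30 against 30 and over. Bring the Abstract, Study design and intervention, and the Discussion into agreement with the method actually used.

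Recruitment began in December 2021 (Trial status), so some patients may already have been allocated. If the fixed rule was applied to them, report this and do not describe them as randomised by permuted blocks. If a random draw decided who was A, say how it was made.

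The cost is a few lines of code and a protocol amendment, with the same staff and patients. The downside is slightly looser balance within small strata: an unfinished block of 4 can leave a stratum two patients out of balance, where an unfinished pair leaves it one out.

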
**Fig. 1 Fig1:**
[figure not shown]
Diagram of the study design

**Fig. 2 Fig2:**
[figure not shown]
Flowchart of enrolment, intervention and assessments. NAFLD: none-alcohol fatty liver disease, WK: week. The “X” refers to time of allocation, intervention and assessment of variables

**Fig. 3 Fig3:**
[figure not shown]

[figure not shown]

[figure not shown]
Standard Protocol Items: Recommendations for Interventional Trials (SPIRIT) chart of the enrollments and assessments during randomized controlled

### Adherence

Individuals will be asked to record their daily intake of probiotic or conventional yogurt in a checklist given them by researchers. To increase compliance and prevent forgetting about daily consumption of probiotic or conventional yogurt, participants will receive short messages on their cell phones every day as a reminder. In addition, each time yogurt packages are delivered, patients will be requested to return empty packages of consumed ones. To ensure the consumption of yogurts by the study participants, and not their family members, additional packages of conventional yogurts will be given to them for probable family members’ use.

### Outcomes

The outcomes of the present clinical trial would be assessment of steatosis, fibrosis, serum liver enzyme levels including aspartate aminotransferase (AST), alanine aminotransferase (ALT), alkaline phosphatase (ALP), Gamma-glutamyl transferase (GGT). Systolic (SBP) and diastolic blood pressure (DBP), lipid profiles including high-density lipoprotein cholesterol (HDL-C), low-density lipoprotein cholesterol (LDL-C), total cholesterol (TC), serum triglycerides (TG) fasting blood sugar (FBS), fasting insulin and glucose hemostasis will also be considered. Weight and BMI will also be assessed. All these measurements will be assessed at study baseline and the end of trial.

### Dietary intake and physical activity assessment

In order to ensure lack of change in dietary intakes of participants during the study, we will collect dietary intake data through the use of a 24-h dietary recall every three weeks throughout the study. These dietary recalls will be distributed through the week days to cover two working days and two weekends. Due to COVID-19 pandemic, dietary recalls will be completed through phone calls, not by face-to-face method. In these phone calls, participants will be asked to report their dietary intakes in a preceding day based on household measures. All reported foods in these recalls will then be converted to grams using available booklets. The average intake based on four dietary recalls will be considered in the analysis.

Participants will be asked not to change their physical activity during the trial. To make sure about this, we will request study subjects to record their physical activity in four separate days throughout the study including two working days and two weekends. All participants will be instructed how to record the type, intensity and time spent in each activity in a certain form that will be given to them at the study baseline. In order to process the physical activity records, we will use earlier published guidelines about MET-h/day values for each type of physical activity, in which we will consider the time spent for a certain physical activity by each participant. All records would be reviewed immediately to find possible errors and the problems will be resolved by interview.

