### Statistical analysis

In this study, all analyses will be done using SPSS software version 26. Normal distribution of data will be assessed by the application of Kolmogorov–Smirnov test. In case of a non-normal distribution, we will apply logarithmic transformation. Results will be reported as mean ± standard deviations (SD) or medians (interquartile ranges). General characteristics and dietary intake of individuals between the two groups will be compared using independent t-test and chi-square test as needed. Repeated measure analysis of variance (RM-ANOVA) will be used to examine the effects of probiotic yogurt consumption on outcome variables, where we will examine the effects of time, intervention as well as time-group interaction effects. In this analysis, baseline values of outcome variables will be controlled for. We will also perform post hoc tests after ANOVA analysis to examine the variables between study groups. In case of any difference between the two groups in terms of dietary intakes (other than the intervention) and physical activity throughout the study, these differences will be adjusted for in the analysis to reach an independent effect of intervention on study outcomes. Statistical significance will be set to 0.05.

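### The in-trial diet and activity data are collected to confirm that habits did not change, but the stated between-arm comparison of in-trial averages cannot by itself show this, and the run-in values are not set against it

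*Protocol article*

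**What the plan says.** The article's section on dietary intake and physical activity assessment gives the reason for the in-trial recalls: "In order to ensure lack of change in dietary intakes of participants during the study". Activity has the same aim: "Participants will be asked not to change their physical activity during the trial. To make sure about this", participants are to "record their physical activity in four separate days throughout the study including two working days and two weekends". Diet is measured by a "24-h dietary recall every three weeks throughout the study", and the summary is fixed: "The average intake based on four dietary recalls will be considered in the analysis".

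The Statistical analysis section gives the comparison: "General characteristics and dietary intake of individuals between the two groups will be compared using independent t-test and chi-square test as needed". It adds that any between-group difference during the study in diet (apart from the intervention) or in activity will be adjusted for when the treatment effect is estimated. The only baseline control it names is for the outcome variables.

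The Study design and intervention section provides a pre-treatment reference. In a two-week run-in, "four 24-h food recalls (two working days and one non-working day) will be used to collect dietary information", and activity is recorded on two days. Nothing in the article sets these values against the in-trial ones.

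**The concern.** The purpose concerns change within people; the stated comparison concerns a difference between arms. These are different questions, and a non-significant answer to the second does not settle the first.

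Three things are at stake.

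- **The statement that habits were maintained.** Everyone adds 300 g/d of yogurt, which may displace other food in both arms. The stated comparison cannot see a shift of that kind. The plan also examines time effects, and a shared dietary shift would be a rival explanation for those.
- **The adjustment rule.** An imbalance in habitual intake that arose by chance before treatment can show up as a difference during the study and so bring a covariate into the outcome model.
- **Efficiency.** A real change in one arm is tested with all the between-person spread left in the error, although run-in values that would remove much of it are already collected.

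**Working it through.** **The plan's own figure.** Treatment lasts 12 weeks with a recall every three weeks: 12/3 = 4 recalls. This agrees with the four recalls that are averaged.

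**What the comparison addresses.** In arm g, write the in-trial mean as F_g = B_g + C_g, where B is habitual (run-in) intake and C is change. The between-arm comparison addresses

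F1 − F0 = (B1 − B0) + (C1 − C0).

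Absence of change means C1 = C0 = 0. If C1 = C0 = c, then c cancels whatever its size. If B1 ≠ B0, the comparison is non-zero even with no change. No assumed figure is needed for either statement.

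**Inputs for the size.**
- From the article: 28 evaluable patients per arm, two-sided 0.05, four in-trial recalls, four run-in recalls (the bracket in that sentence lists only three days; four is used here).
- Assumed: between-person SD of 1 and a within-to-between-person variance ratio r of 1, 2 or 3. The article gives no value.
- A mean of four recalls then has variance v = 1 + r/4. The correlation between run-in and in-trial means is ρ = 1/v.

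**Change of 0.5 SD in one arm.**
- t-test on in-trial averages: SE = √(2v/28).
- ANCOVA on the run-in value: SE = √(2v(1 − ρ²)/28).

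**Change of 0.5 SD shared by both arms.** Each person's change has variance 2 × r/4 = r/2, so a paired test on all 56 has SE = √((r/2)/56). The between-arm t-test stays at its nominal 5%.

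| r | v | ρ | SE, t-test | Power, t-test | SE, ANCOVA | Power, ANCOVA | SE, paired | Power, paired (shared shift) |
|---|---|---|---|---|---|---|---|---|
| 1 | 1.25 | 0.80 | 0.299 | 38% | 0.179 | 78% | 0.094 | >99% |
| 2 | 1.50 | 0.67 | 0.327 | 32% | 0.244 | 52% | 0.134 | 96% |
| 3 | 1.75 | 0.57 | 0.354 | 28% | 0.290 | 39.5% | 0.164 | 85% |

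Simulation agrees within its error: 29 to 39% against 38 to 79% for the one-arm change, and about 5% against 85 to 100% for the shared shift. For activity there are only two run-in days. Simulation then gives 37, 33 and 28% against 65, 44 and 34% for the one-arm change (r = 1, 2, 3).

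**Chance habitual imbalance, no change.** Under randomisation B1 − B0 has SE √(2/28) = 0.267 SD. An imbalance of at least 0.5 SD in either direction has z = 0.5/0.267 = 1.87, a probability of about 6% per nutrient. With 34 per arm, √(2/34) = 0.243 and z = 2.06, about 4%. Given a realised imbalance of exactly 0.5 SD, the t-test flags a difference in about 25, 22 and 20% of trials for r = 1, 2, 3.

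**The case against.** The strongest reply is that the trial estimates a between-arm effect, so a between-arm check is what matters. Both arms eat the same amount of yogurt, and any shift common to both cancels from the treatment comparison. That stands. A reader might infer that an unseen shared shift biases the yogurt effect; the design does not support that. The shared shift bears only on the statement that habits did not change and on the within-group time effects.

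It is also fair that randomisation rules out a habitual difference in expectation. A reader might infer that false flags would be common. They would not: the flag rates above are conditional on an imbalance with about a 6% chance per nutrient, and with neither change nor population difference the t-test flags the usual 5%. When a chance imbalance is flagged, the consequence is adjustment for an imbalance that exists, not a false claim about yogurt.

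Third, the wording is loose. The sentence naming the t-test gives no time point for dietary intake, so it may cover a baseline comparison of run-in intake, and it names no test for activity. It would therefore go too far to say that the run-in data are certainly unused, or that a wrong test is specified for activity. But comparing run-in intake between arms is still not comparing run-in with in-trial intake.

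Finally, extra table columns are detail that an article may leave to a fuller document. The point does not rest on their absence: the article itself states the purpose, the summary and the between-arm comparison, and these do not match.

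**Conclusion.** The point holds as a limited one. The stated comparison is suitable for finding imbalance between arms but does not by itself show that diet and activity were unchanged. That follows from the algebra alone.

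The efficiency loss depends on the assumed variance ratio. For a 0.5-SD change in one arm with 28 per arm, power is about 29 to 39% as written and 38 to 79% with ANCOVA on the run-in value, over ratios of 3 down to 1. The gain is small at a ratio of 3 and large at 1.

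No outcome, primary estimate or sample size is affected. The change is worth making because it is nearly free and touches both the claim of unchanged habits and the rule that turns any between-arm difference into covariate adjustment. Whether the treatment model should adjust for diet measured after randomisation at all is a separate question.

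**What to change.** In the section on dietary intake and physical activity assessment and in Statistical analysis, for energy, main nutrients and MET-h/day:

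1. Report the mean change from run-in to the in-trial average in each arm, with 95% CI.
2. Compare arms by ANCOVA of the in-trial average on the run-in value, with 95% CI.
3. Call diet or activity unchanged or similar only as far as those intervals allow, not because p > 0.05.
4. State the time point to which the t-test on dietary intake applies, and keep that test for describing baseline.

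The cost is analysis wording and a few table columns, with no new data, visits or patients. The one downside is that any shared change will be visible and must be reported.
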